### Outcome assessment

Outcomes will all be assessed via a booklet of self-administered questionnaires that will be mailed to participants prior to the initial physical examination and at each of the follow-up points (5 weeks, 10 weeks, 26 weeks and 52 weeks post randomisation). Participants will return completed follow-up questionnaires to the researchers via mail marked only with their participant identification number. The outcomes to be measured in the trial are summarised in Table 3.

**Table 3 T3:** Outcome measures

Outcome measure	Measurement point (weeks)

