### Data analysis

Data analysis will focus on detecting the between-group treatment effect (with 95% confidence intervals) at each of the follow-up points (5 weeks, 10 weeks, 26 weeks and 52 weeks following randomisation). Analyses will be conducted using PASW Version 18^b^, with alpha set at 0.05 using a two-tailed hypothesis. Continuous data will be analysed using linear mixed models (with the group x time interaction estimating the treatment effect). These were chosen for their strength in analysing longitudinal biological data and accounting for correlations associated with repeated measurements [104-106]. The mixed models will adjust for the baseline score of the outcome of interest, along with the stratification variables (treatment centre and subgroup) as recommended by the revised CONSORT statement [107]. The inclusion of treatment centre as a random effect will account for the potential clustering of outcomes within treatment centres [108,109]. In addition, the mixed models will adjust for gender and Orebro Musculoskeletal Pain Questionnaire score, as gender and psychosocial factors are considered to be important prognostic factors [107]. Ordinal data will be analysed using the Mann Whitney U test.

At each follow-up point, participants in each group will be dichotomised according to whether they achieved the minimum clinically important difference of the outcome or not, and then the risk ratio, risk difference and number needed to treat will be calculated along with 95% confidence intervals [107,110]. Statistical significance will be evaluated using Chi square analysis. For these purposes, the minimum clinically important difference will be defined as 10/100 for the Oswestry [111], 2/10 for the NRS pain scales [111], at least "much improved" on the global rating of change scale [71,112] and "very satisfied" on the treatment satisfaction scales [71]. It has been argued that these values for minimum clinically important difference may be too low in some contexts [113], hence we will repeat this analysis using a threshold of 50% reduction in Oswestry scores and NRS pain scores based on empirical validation studies suggesting that this may be a more suitable threshold for important differences [67,114].

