All data will be analysed on an intention to treat basis, in that all participants will be analysed in the treatment group to which they are initially allocated regardless of their compliance with that treatment [107,115]. All participants who withdraw from treatment for any reason will continue to be contacted for follow-up assessments and informed that their data are still required. Our primary method of analysis will not impute missing data [116]. This is justified as all methods of data imputation have limitations [107], and the linear mixed model analysis that we planned for analysing continuous data is thought to inherently account for missing data in a more effective and less biased manner than data imputation methods [105,106,117,118]. However, given the popularity of simple data imputation methods [105,107] we will undertake a secondary sensitivity analysis to determine whether the results would differ if missing data were replaced using the last observation carried forward method.

In addition to the analyses described above, subgroup analyses will be undertaken to estimate the effects of specific treatment on each of the five subgroups within the trial. This will be possible due to the stratification of the randomisation for subgroup which will ensure that each subgroup has a balanced allocation of participants between the specific treatment and advice groups. Preliminary analysis will need to be undertaken on two of the subgroups prior to the completion of the trial in order for PhD thesis submission deadlines to be met. It is often recommended that an alpha adjustment be made when interim analyses are to be performed [107,119]. However, in our trial the overall data from all trial participants will not be analysed prior to the completion of recruitment, so no adjustment in alpha will be made in the final analysis involving all participants.

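### The no-imputation rule is justified for missing follow-up outcomes only; as written it also drops participants who lack a baseline covariate (minor)

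*Protocol article*

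**What the plan says.** All of this is in the protocol article, mainly under Data analysis.

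- **Missing data.** "Our primary method of analysis will not impute missing data". Part of the reason given is that the mixed model "is thought to inherently account for missing data in a more effective and less biased manner than data imputation methods". Neither statement separates outcomes from covariates. The only sensitivity analysis named for missing data is last observation carried forward.
- **Covariates.** "The mixed models will adjust for the baseline score of the outcome of interest", together with treatment centre and subgroup. In addition, "the mixed models will adjust for gender and Orebro Musculoskeletal Pain Questionnaire score". The time point of the Orebro covariate is not stated. Baseline is the natural reading, since it is included as a prognostic factor.
- **Intention to treat.** "all participants will be analysed in the treatment group to which they are initially allocated regardless of their compliance with that treatment".
- **Source of the baseline values.** Under Outcome assessment, a self-completed booklet is "mailed to participants prior to the initial physical examination" and again at each follow-up.

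**The concern.** A likelihood-based mixed model uses whatever outcome values a participant has, so a missed follow-up visit does not remove that person. It has no such provision for covariates: a row with a missing covariate cannot enter the likelihood and is deleted. A baseline covariate is the same at every visit, so all of that participant's rows go. The reason given for not imputing therefore covers only part of what the sentence rules out.

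A participant who returns all four follow-up booklets but has an unscorable baseline Orebro would be lost from the Oswestry, back-pain and leg-pain models. One who lacks only the baseline score of a single outcome would be lost from that outcome's model. What is at stake is precision and the completeness of the analysed set. The between-group contrast itself is not at risk of bias from this, because baseline values are collected before allocation.

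**Working it through.** **1. Does the article prevent or repair the gap?**

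- *Randomisation and allocation*: to enrol a participant, the physiotherapist sends name, date of birth, subgroup and centre. A complete baseline booklet is not listed as a condition.
- *Classification*: the Orebro score decides membership only for people who fit none of the other four subgroups. A missing score would not by itself keep someone out of those four.
- *Exclusion criteria*: one pain score is needed for screening. This does not secure both the back and the leg rating, nor the Oswestry.
- *Data integrity*: omissions are checked as possible entry errors and settled with the person entering the data, not with the participant.
- *Last observation carried forward*: nothing precedes baseline, so it cannot fill a baseline value.

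A missing baseline value is therefore possible, and no stated step recovers it.

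**2. The mechanism.** A trial of 250 with four complete follow-ups each (1,000 rows) was simulated. Five participants lacked the baseline score and five others lacked Orebro. The mixed model with group by time, baseline score and Orebro used 240 participants and 960 rows. All ten were lost despite complete outcomes.

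**3. The plan's own sample size.** Inputs from Sample size: difference 10, SD 20, two-sided alpha 0.05, power 80%. A two-sample t-test with d = 10/20 = 0.5 needs 63.77, so 64 per group and 128 in total. The stated figure is reproduced.

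**4. Participants lost and power.** The article gives no rate of missing baseline values, so p, the share lacking either covariate, is an assumption. Lost = 250 × p. Power = Φ(10 / (20 × √(2/n)) − 1.96), with n per group = 250 × (1 − p)/2. This takes follow-up as complete and ignores any gain from adjustment.

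| p | lost | n per group | power |
|---|---|---|---|
| 0% | 0 | 125 | 97.7% |
| 2% | 5 | 122.5 | 97.5% |
| 5% | 12.5 | 118.75 | 97.1% |
| 10% | 25 | 112.5 | 96.3% |

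About 122 of 250 (1 − 128/250 = 48.8%) would have to be lost before the total fell to 128. If each covariate were missing independently at rate a, the loss would be 250 × (1 − (1 − a)²): about 5, 10 or 24 participants at a = 1%, 2% or 5%.

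**5. Variance and bias.** Trials of 250 (1:1) were simulated with a true effect of 0.5 SD, covariates explaining 20% or 35% of outcome variance, and missingness rising with severity. Deletion was compared with filling the pooled baseline mean.

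| p | extra variance under deletion |
|---|---|
| 2% | about 1-2% |
| 5% | about 3-5% |
| 10% | about 7-10% |

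The mean estimate was 0.50 under both methods. As a plausibility check, if the fill cost nothing at all, the variance ratio would be roughly 1/(1 − p): 1.020, 1.053 and 1.111. The simulated figures sit at or below these.

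**The case against.** **The intention-to-treat rule is not contradicted.** A reader might infer that dropping these participants breaks the statement that "all participants will be analysed in the treatment group to which they are initially allocated". The full sentence, however, is about allocated group and compliance, and the same paragraph openly says that missing data will not be imputed. It does not promise that every randomised participant enters every model. The fix below does not deliver that either, since it needs at least one follow-up value. This objection stands.

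**The rule may be meant for follow-up data only.** It comes just after the sentence on following up people who withdraw and is followed by last observation carried forward. That is a fair reading of intent. The sentence is nevertheless unqualified, and an analyst following it literally would delete these participants.

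**Handling of missing covariates is usually left to the analysis plan.** This is true of an article that says nothing on the matter. Here a rule is stated, and an analysis plan that filled baseline values would depart from its wording. The point is the breadth of the rule, not an omission.

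**Few values may be missing.** Baseline booklets go out before the examination and hence before randomisation, and some scores feed screening or classification. A reader might take the replacement of the Oswestry sex-life item as a sign that skipped items are expected. It concerns one item, was made to prevent gaps, and says nothing about Orebro. The missing rate is simply unknown.

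**Analysed sets differ between outcomes anyway.** This also stands: it happens in any analysis without imputation and is not a separate fault here.

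**Conclusion.** The point holds as a minor one. The stated reason, that the mixed model "is thought to inherently account for missing data in a more effective and less biased manner than data imputation methods", covers missing outcomes and does not extend to the two questionnaire covariates in every continuous model. Whenever such a value is missing, a participant with observed follow-up is lost.

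The size is small at any plausible rate: at an assumed 10% missing, 25 of 250 participants, 7-10% more variance, and power of 96.3% instead of 97.7%. The loss of precision matters somewhat more in the subgroup analyses, but the article already calls those likely underpowered, and a few per cent of variance does not change that.

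Two stronger readings are not supported: that the plan contradicts its own intention-to-treat rule, and that the treatment effect would be biased. The conclusion assumes that the Orebro covariate is the baseline value, that the no-imputation sentence is applied literally, and that the missing rate lies in the range shown.

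**What to change.** Limit the rule and its reason to outcomes, and add a rule for baseline covariates. Suggested wording:

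> Missing follow-up outcomes will not be imputed in the primary analysis, because the linear mixed model uses all observed outcomes under a missing-at-random assumption. A missing baseline covariate (the baseline score of the outcome, or baseline Orebro) will be replaced by the mean of the observed baseline values pooled over both groups, without use of allocation or follow-up data. Every randomised participant with at least one follow-up value will be included in the model.

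This also settles the time point of the Orebro covariate. The pooled mean is one acceptable choice. A missing-value indicator, modelling baseline as part of the outcome vector, or requiring complete baseline covariates before randomisation would also close the gap.

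The cost is a sentence or two of text and a line of code, with no new data and no extra participants. The downside is slightly weaker covariate adjustment for the few participants whose value is filled. As the fill uses only pre-allocation data, it does not bias the comparison between groups.

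### The no-imputation rule leaves the responder and ordinal analyses complete-case without a supporting reason, and the only missing-data check, LOCF, cannot test missing at random

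*Protocol article*

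**What the plan says.** The missing-data rule stands in the Data analysis section of the protocol article. The paragraph opens "All data will be analysed on an intention to treat basis" and then states "Our primary method of analysis will not impute missing data". Two reasons follow. The general one is "This is justified as all methods of data imputation have limitations". The specific one is that "the linear mixed model analysis that we planned for analysing continuous data is thought to inherently account for missing data", and does so better than imputation would.

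One sensitivity analysis is planned, "given the popularity of simple data imputation methods": it will show whether the results change "if missing data were replaced using the last observation carried forward method".

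Earlier in the same section, two families of analysis are set up that are not mixed models:

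- Ordinal outcomes: "Ordinal data will be analysed using the Mann Whitney U test".
- Responder outcomes at each follow-up: chi-square tests, with number needed to treat, risk difference and risk ratio. These cover the Oswestry (10 points), both pain scales (2 points), global change and the satisfaction scales. The Oswestry and pain analyses are repeated with a 50% reduction as the threshold.

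No separate missing-data rule is given for either family.

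**The concern.** A mixed model fitted to all visits uses a participant's observed scores even when a later one is missing, and is valid if data are missing at random given what was observed. A chi-square or rank test at one visit has no such property. Without imputation it drops everyone missing at that visit and relies on those who remain being representative of their arm, which is generally a stronger assumption. The general reason given for not imputing does not help, because dropping participants has limitations too.

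The responder analysis is not marginal. It restates all three primary outcomes in the form that many readers will use, and it yields the number needed to treat. The same Oswestry data would be analysed under two different missing-data assumptions, so the two results could diverge for that reason alone.

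The sensitivity analysis does not fill the gap. The plan already ranks the mixed model above imputation methods for bias, so a disagreement with LOCF would be put down to LOCF. Agreement would leave missing at random untested.

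**Working it through.** **1. What each analysis does with a participant seen at weeks 5, 10 and 26 but missing at week 52**

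| Outcome type | Planned analysis | Week-52 comparison without imputation |
|---|---|---|
| Continuous | Linear mixed model | Earlier scores contribute |
| Ordinal | Mann-Whitney | Participant dropped |
| Responder | Chi-square, risk ratio, risk difference, number needed to treat | Participant dropped |

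Under LOCF there is a further gap. Table 3 lists no baseline measurement for global change or the two satisfaction scales, so anyone lost before week 5 has no value to carry forward.

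**2. The plan's own figure**

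The plan gives no figure for missing data. Its sample size (10 points, SD 20, two-sided 0.05, 80% power) reproduces: the normal formula gives 2 × (1.96 + 0.84)² × 20² / 10² ≈ 62.8, so 63 per group. The t-based value is 63.77, so 64 per group and 128 in total, as stated. With 250 recruited, power for 10 points is 97.7% with no loss and 94.2% with an assumed 20% loss. The issue is therefore bias, not power.

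**3. LOCF by hand, no true effect**

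Assumed mean Oswestry in both arms at weeks 0, 5, 10, 26 and 52: 30, 24, 20, 17, 15. The loss rates are also assumed.

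Spurious difference (advice minus specific) = (loss in advice − loss in specific) × (mean at the frozen visit − week-52 mean)

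| Loss, advice v specific | Frozen at | Spurious difference (points) |
|---|---|---|
| 15% v 10% | week 5 | 0.05 × (24 − 15) = 0.45 |
| 20% v 10% | week 5 | 0.10 × (24 − 15) = 0.9 |
| 20% v 10% | baseline | 0.10 × (30 − 15) = 1.5 |
| 25% v 10% | baseline | 0.15 × (30 − 15) = 2.25 |
| equal | any | 0 |

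If the heavier loss is in the specific arm, the sign reverses.

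**4. Simulation, with loss spread over the visits**

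SD 20 is from the Sample size section. Assumed: correlation 0.6 between visits; advice means 40, 34, 30, 27, 25; specific means either the same or 40, 31, 24, 19, 15. Week-52 results under LOCF:

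| True difference | Loss, advice v specific | LOCF difference |
|---|---|---|
| 0 | 20% v 20%, unrelated to outcome | about 0 |
| 0 | 20% v 10%, unrelated to outcome | 0.8 |
| 0 | 34% v 12%, related to previous score | 2.9 (risk difference 0.082) |
| 10 | 20% v 20%, unrelated to outcome | 8.8 |
| 10 | 34% v 11%, related to previous score | 12.3 |

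So LOCF can inflate, shrink or leave the difference alone. In the third setting, regression imputation under missing at random gave 0.05 points and a risk difference of 0.002. Even with equal loss of 20% and no bias in the difference, LOCF lowered the advice responder rate from 0.61 to 0.56.

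**5. Complete-case responder analysis, same assumptions**

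- Loss unrelated to outcome: essentially no bias.
- Loss related to previous score, 34% v 11%: a true risk difference of 0.188 becomes 0.198.
- Loss related to change since baseline: 0.190 becomes 0.183 (24% v 24%) or 0.169 (24% v 13%), and 0.189 becomes 0.153 (35% v 13%).
- As the last, but with the mechanism running in opposite directions in the two arms (24% v 24%): 0.188 becomes 0.131.
- No true effect, loss related to change: bias from about 0 to −0.07.

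**The case against.** Several stronger readings are tempting, and the document does not support them.

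- A reader might infer that no reason at all is offered for the non-model tests. The general remark about the limits of imputation is not tied to any model. It is weak support for dropping participants, but it is there. That the rule reaches these tests is itself a reading of the paragraph's opening words and of the absence of another rule, though it is the natural reading.
- A reader might infer that complete-case tests break a promise. The sentence says that "all participants will be analysed in the treatment group to which they are initially allocated regardless of their compliance with that treatment". It defines groups by allocation; it does not promise complete data.
- A reader might infer that unequal loss is to be expected, since participants are unblinded and sessions number ten against two. Outcomes come by mailed questionnaire on the same schedule in both arms, and those who withdraw from treatment will still be followed. Unequal loss is possible, not shown to be likely.
- A reader might add that LOCF understates standard errors. Nothing calculated here bears on that, and the point does not need it.

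It is also fair to say that LOCF is labelled secondary, that the main analysis of the three primary outcomes is untouched, and that recovery may be slower than assumed above: the Background notes slower spontaneous recovery at the subacute stage and frequent persistence or recurrence. All of this limits the size of the problem.

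Finally, imputation details are often left to an analysis plan that is not shown. But this point concerns what the article itself fixes: no imputation for all data, and LOCF as the check. On those, the objection does not succeed.

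**Conclusion.** The point holds in a limited form. The substantive reason for not imputing covers the continuous outcomes only, and the ordinal and responder analyses, including the responder versions of all three primary outcomes, are left complete-case. The only check on missing data is one that does not probe missing at random and that typically holds lost participants at worse scores where the plan expects improvement.

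Bias in the LOCF treatment difference requires loss or improvement to differ by arm, and it can go either way. With no true effect, the hand illustration gives about 0.5 to 2.3 Oswestry points, at most about a quarter of the 10-point threshold, and nil with equal loss. The complete-case risk difference moved by between almost nothing and about 0.07, depending on why participants were lost. Every mean, loss rate, correlation and loss mechanism behind these figures is an assumption, apart from the SD of 20. They show a range and predict nothing about this trial. The change should be made, but the main mixed-model result does not depend on it.

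**What to change.** - Keep the mixed model without imputation as the main analysis of continuous outcomes, and limit the mixed-model justification to those outcomes.
- For responder and ordinal outcomes, use multiple imputation by arm, with baseline values, the stratification factors and all observed visits in the imputation model. Derive responder status from the imputed scores.
- Replace LOCF, or demote it to a supplementary analysis, with a delta-adjusted sensitivity analysis for the three primary outcomes. Shift the imputed values over a prespecified range, varied in each arm, and report where the conclusion changes.

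The cost is revised wording and some extra programming. No new data are needed and the sample size does not change.

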### Sample size

We will recruit a total sample size of at least 250 participants. We would require 128 participants (64 in each group) to detect the minimum clinically important difference between groups of 10% on the Oswestry assuming a standard deviation of 20 (two tailed hypothesis, alpha = 0.05, power = 80%) [120]. However, we wish to recruit more than this to improve power in our planned subgroup analyses. We acknowledge that the subgroup analyses are likely to remain underpowered [121], but they may provide some guidance for future research targeting the subgroups with greatest feasibility and effectiveness.

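### Subgroup results are meant to point to the most responsive subgroups, but no stated analysis compares treatment effects between subgroups

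*Protocol article*

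**What the plan says.** All references are to the protocol article.

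- **Data analysis, subgroup plan.** Beyond the overall analyses, "subgroup analyses will be undertaken to estimate the effects of specific treatment on each of the five subgroups within the trial". Two of the subgroups will have a preliminary analysis before the trial is complete, for thesis deadlines.
- **Data analysis, model.** Continuous outcomes go into linear mixed models "with the group x time interaction estimating the treatment effect". The models adjust for the baseline score "along with the stratification variables (treatment centre and subgroup) as recommended by the revised CONSORT statement", and also for gender and Orebro score. Group x time is the only interaction named. Analyses are run "with alpha set at 0.05 using a two-tailed hypothesis", with 95% confidence intervals.
- **Sample size.** "We would require 128 participants (64 in each group) to detect the minimum clinically important difference between groups of 10% on the Oswestry", with an SD of 20 and 80% power. The target is raised to at least 250 to give the subgroup analyses more power. The section concedes that they will probably still be underpowered, and adds that "they may provide some guidance for future research targeting the subgroups with greatest feasibility and effectiveness".

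**The concern.** The stated use and the stated analysis do not match. To say where effectiveness is greatest is to compare treatment effects across subgroups. What is described is an effect within each subgroup, plus a model in which subgroup shifts the mean outcome but does not modify the treatment effect. Nothing stated measures whether the five effects differ by more than chance.

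With about 50 people per subgroup, estimates will scatter widely even if the true effects are the same. A reader who looks for the subgroups that reached significance, or simply for the largest estimates, will usually see a contrast. Later research could then be directed to some subgroups and away from others on sampling noise. The overall comparison of specific physiotherapy with advice is not affected.

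**Working it through.** **Inputs from the article:** difference 10 Oswestry points, SD 20, two-sided alpha 0.05, total of at least 250, five subgroups, balanced allocation within subgroup. **Assumption:** equal subgroup sizes, 250 / 5 = 50, so 25 per arm. The article gives no expected sizes.

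**1. The article's own figure.** With 64 per arm, the noncentrality is 10 / (20 × √(2/64)) = 2.83 and t-test power is 80.1%; with 63 per arm it is 79.5%. The stated 128 is reproduced.

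**2. Power in one subgroup.** SE = 20 × √(2/25) = 5.66 points. Noncentrality = 10 / 5.66 = 1.77 on 48 df, giving power p = 0.410. The 95% CI half-width is 2.011 × 5.66 = 11.4 points, wider than the 10-point effect.

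**3. Identical 10-point effect in all five subgroups, each read as significant or not.**
- All five significant: 0.410^5 = 0.012
- None significant: 0.590^5 = 0.071
- Mixed picture: 1 − 0.012 − 0.071 = 0.917

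**4. Dependence on the common true effect** (SD 20, equal subgroups, same formula):

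| Common true effect (points) | Mixed pattern |
|---|---|
| 0 | 23% |
| 3 | 35% |
| 5 | 53% |
| 7.5 | 77% |
| 10 | 92% |
| 12 | 93% |
| 15 | 78% |
| 20 | 29% |

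The first row is essentially the chance that at least one subgroup is significant when there is no effect anywhere: 1 − 0.95^5 = 0.226, for one outcome at one visit.

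**5. Sensitivity at 10 points.** The mixed figure is 93–94% for four assumed sets of unequal subgroup sizes, 87–90% with an assumed 10–20% dropout, and 85–94% with an assumed baseline correlation of 0.3–0.7.

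**6. No p-values, estimates only.** With five independent estimates and identical true effects of any size, the expected gap between best and worst is 2.326 × SE. Adjusting for a baseline score with correlation r multiplies the SD by √(1 − r²).

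| Baseline correlation (assumed) | SE | Mean gap, best to worst | Gap above 10 points |
|---|---|---|---|
| none | 5.66 | 13.2 | 72% |
| 0.5 | 4.90 | 11.4 | 60% |
| 0.7 | 4.04 | 9.4 | 40% |

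**7. What an interaction test would do.** In a simulation of 40,000 trials with a 4-df group x subgroup F test at 25 per arm per subgroup, identical 10-point effects led to declared heterogeneity in about 5% of trials. Power was about 29% for true effects of 10, 10, 10, 0, 0 and about 48% for 20, 10, 10, 10, 0.

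**The case against.** **The article is silent rather than wrong.** It is condensed, no analysis plan is shown, and the subgroup sentence names no model. Five subgroup effects are also what a group x subgroup model yields. A reader might infer that the plan has ruled out an interaction, or has committed to five separate analyses in the final report; the text supports neither. The early look at two subgroups cannot include all five, but it does not fix the final analysis. What stands against this objection is that the article does state the purpose, a between-subgroup judgement, and lists its model terms without one that serves it.

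**There is no p-value rule.** A reader might infer that subgroups will be sorted by significance. No passage says so: the wording is to estimate, with confidence intervals. The alpha of 0.05 has no stated exception for subgroups, and the larger sample is justified by power, which is a property of tests, but that is not a decision rule. The 92% therefore applies only if results are read that way. Step 6 does not need that reading.

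**Low power is disclosed and the aim is modest.** This is true, and the article deserves credit for it. But low power is the reason the estimates scatter, and guidance on which subgroups to pursue is the very inference at risk.

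**Each subgroup has its own protocol.** Whether a given protocol beats advice is a fair question that needs no interaction test. This stands: the subgroup-specific estimates should be kept. It does not extend to saying that one protocol works better than another.

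**Conclusion.** The point holds, and it is limited to the gap between purpose and method: the article wants to learn where treatment works best and states no comparison that could show it. It would be too strong to say that identical effects almost always look different. That is so near the planned effect (92–93% at 10–12 points) but not at 5 points (53%) or 20 points (29%), and only on a significance reading. On estimates alone, a spurious gap of more than 10 points, the article's own important difference, appears in 72% of trials unadjusted, and in 60% or 40% with assumed baseline correlations of 0.5 or 0.7. These figures rest on equal subgroups of 25 per arm and an SD of 20. The change should be made, though the main trial result does not depend on it.

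**What to change.** Add group x subgroup, and group x subgroup x time with its lower-order terms, to the mixed model. Report the interaction for the Oswestry, naming in advance the visit to which it refers. Take the five subgroup effects with 95% CIs from that model and label them exploratory. State that any claim of differing effectiveness will rest on the interaction, not on which subgroups reach significance or rank highest. The early report on two subgroups, which cannot draw on all five, should make no such claim.

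The cost is a few model terms and a short statement, with no new data. The real drawback is that the interaction test is weak at 250 participants (about 29–48% power in the scenarios examined): it guards against false differences but will often miss true ones. The plan should therefore also say that a non-significant interaction is not evidence of equal effects. Estimates of each protocol against advice remain reportable.
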